### Analysis

Primarily, no inferential statistics are planned. In the early research stage, the focus is on descriptive questions. The description is carried out by determining minima and maxima, mean value, SD and variance, median and IQR, correlations, interrater stability, and signal-to-noise ratio. In the event of a termination of data collection due to external circumstances such as air sickness, all data recorded up to that point are analyzed. Multiple imputation compensates for missing values.

Statistical analyses will be carried out using R software (version 4.4.1 or later, open source; R Project for Statistical Computing) and Python (version 3.12.4 or later, open source; Python Software Foundation). The research team will carry out the data analysis.

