## Methods

### Overview

The study aims to collect intra- and interindividual multiaxial movement (angular velocity, measured using gyroscopes, and acceleration, measured using synchronous, using synchronous accelerometers [6-DOF sensors]) and electrocardiogram (ECG) data at different gravitational states (µ*g* to hypergravity) under physiological real-life conditions in parabolic flights. The data will be used to describe acceleration artifacts caused by the sensors’ physical rolling, yawing, and pitching movements on the body surface. ARTIFACTS is designed as an open, prospective, noninterventional, noninvasive, nonrandomized, descriptive study. The procedure, including the experiment, will be identical for all participants. For this reason, blinding is not appropriate. The study will last 10 months (September 2024 to July 2025). The data collection will take approximately 3 weeks.

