### Study Objectives

The primary end point comprises the description of acceleration artifacts (morphology and expression), differences in accelerations or angular velocities, and the identification of variables that affect acceleration sensors due to gravitational acceleration. The evaluation of signal filtering and peak detection algorithms are the secondary end points of this study. Of particular interest are differences in motion trajectory resulting from SCG-BCG data to describe and quantify the influence of artifact formation, more specifically dedicated consideration of the differences in accelerations and angular velocities in 6 spatial dimensions on 2 different body locations in µ*g*, 1*g*, max 1.8*g*, and transitions.

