### Participants

In ARTIFACTS, 4 healthy adult persons (male and female; 18-65 years old, fit for duty) without structural heart disease and in stable sinus rhythm will be included. Participants who are unwilling or unable to participate; who have an addiction, heart or cardiovascular disease, mental illness or panic disorders, allergy or intolerance to electrode gel or wound dressings, emphysema, and multimorbidity (ie, co-occurrence of at least 2 chronic conditions); or who are breastfeeding or pregnant will be excluded from the study. Recruitment takes place via personal contact. All study participants are members of the scientific group. Recruitment is done on a strictly voluntary basis. The project’s explorative and hypothesis-generating approach justifies the number of cases. The project is a data collection of heart-healthy individuals in the form of an observational study to generate hypotheses on detecting and eliminating acceleration artifacts due to the self-rotation of the 6-DOF sensors and their differentiation from heart-induced body acceleration. Four participants (3 male and 1 female) are sufficient for (1) evaluating the feasibility of the measuring or recording method, (2) obtaining data for postanalysis, (3) determining variation in individual biophysical vibrations related to the cardiovascular system, and (4) having sufficient backup personnel for dropouts, for example, due to sudden illness. The participants are a convenience sample of the study personnel. There are no financial expenses for the participants in this study.

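### The Analysis section sets an unscoped multiple-imputation rule in a four-person, primarily descriptive signal study, so model-generated values could enter the description of artifacts

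*Protocol article*

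**What the plan says.** Three statements in the Analysis section of the protocol article matter here.

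- On inference: "Primarily, no inferential statistics are planned".
- On outputs: "The description is carried out by determining minima and maxima, mean value, SD and variance, median and IQR, correlations, interrater stability, and signal-to-noise ratio".
- On incomplete data, when collection ends early, for example through air sickness: "all data recorded up to that point are analyzed. Multiple imputation compensates for missing values". These are two separate sentences, one directly after the other.

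The imputation sentence has no qualifier. It does not say what is imputed, at what level, or for which cause of loss.

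Other sections give the context. Overview: "ARTIFACTS is designed as an open, prospective, noninterventional, noninvasive, nonrandomized, descriptive study". Study Objectives opens with "The primary end point comprises the description of acceleration artifacts (morphology and expression" and adds differences in accelerations or angular velocities. Participants fixes the sample at four and gives a non-statistical reason: "The project’s explorative and hypothesis-generating approach justifies the number of cases". Measurements lists sex, age, the six-axis motion signals, heart rate and gravity level as the recorded variables. Study Procedure adds weight, height and BMI. Ethical Considerations says that motion sickness stops the experiment.

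**The concern.** The article names a method, and the method fits the study poorly. This is different from leaving a detail to an analysis plan.

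Multiple imputation is mainly used to carry the uncertainty from missing data into an inferential estimate, and primarily no such estimate is planned. The planned outputs include minima, maxima and signal-to-noise ratio, and the end point concerns the shape and strength of an artifact. An imputed waveform shows what the imputation model assumes and is not an observation of an artifact.

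There is also a risk of circularity. The Hypothesis section expects the artifact to be absent at 0*g* and stronger at 1.8*g*. An imputation model that uses gravity level would feed an assumed link between gravity and acceleration into the description meant to reveal that link. A model that ignores gravity level would blur the states being compared.

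At stake are the reported SD, variance, extremes, correlations and signal-to-noise ratio, and the reader's view of how much was actually measured.

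**Working it through.** **1. Could the rule reach the signals?** Early termination is the only source of missing data that the Analysis section names, and it removes recordings. The signals are the main recorded variables. Sex, age and body size are unlikely to be missing for four members of the research team. So the signals are plausibly within reach of the sentence. The text neither includes nor excludes them.

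**2. The planned amount of data.** Schedule gives 3 flights × 30 parabolas = 90. The participant-role totals in Table 1 are 30 + 20 + 20 + 20 = 90, so the plan's figure reproduces. Participants 2, 3 and 4 are each measured on one flight, for 20 parabolas.

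**3. The possible share of imputed data.** Suppose one of participants 2 to 4 stops after *k* of 20 parabolas and every lost parabola is imputed. The share of that person's data is (20 − *k*)/20, and the share of all data is (20 − *k*)/90. The values of *k* are assumptions.

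| Stop after *k* | Parabolas lost | Share of own data | Share of all 90 |
|---|---|---|---|
| 1 | 19 | 95% | 21.1% |
| 5 | 15 | 75% | 16.7% |
| 10 | 10 | 50% | 11.1% |
| 15 | 5 | 25% | 5.6% |

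With recorded data only, a stop after 5 leaves 5 real parabolas for that person and 90 − 15 = 75 overall.

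**4. What imputation would do to the listed statistics.** This is an illustration on assumed inputs that are not in the documents. There is one amplitude per parabola, normally distributed with mean 1 and SD 0.2, and 20 parabolas are planned. Lost values are imputed 20 times from a normal model fitted to the same person's recorded parabolas, with parameter uncertainty drawn properly. There are 4,000 repetitions. The setting favours imputation, because the model form is correct and the loss is unrelated to the values.

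| Stop after | RMSE of mean: recorded / imputed | Average SD: recorded / imputed | Average maximum: recorded / imputed |
|---|---|---|---|
| 3 | 0.117 / 0.138 | 0.178 / 0.300 | 1.17 / 1.57 |
| 5 | 0.089 / 0.093 | 0.189 / 0.228 | 1.23 / 1.43 |
| 10 | 0.062 / 0.063 | 0.193 / 0.203 | 1.31 / 1.39 |
| 15 | 0.0516 / 0.0518 | 0.196 / 0.199 | 1.35 / 1.38 |

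With all 20 parabolas the average SD is 0.198 and the average maximum is 1.37. Imputation adds no information on the mean. It inflates the SD when few parabolas were recorded, and it moves the maximum.

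**The case against.** A reader might infer that the protocol prescribes imputation of the recordings lost when a flight is stopped, so that synthetic signal would certainly enter the primary description. The documents do not support this. The sentence on termination reads by itself as an available-data rule. The imputation sentence is separate, and the link between them is inferred from their being adjacent. The missing values could be short dropouts or gaps in non-signal variables. The defensible word is *could*.

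Other points on the plan's side also carry weight:

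- The study is not purely descriptive. The text says only that inference is not primarily planned.
- The imputation model may properly be left to an analysis plan, and its absence from a condensed article is no fault.
- Means, variances and correlations can be averaged across imputations. The difficulty lies mainly with extremes and morphology.
- Scattered gaps could be filled from many beats of the same person, without borrowing from others.
- In the illustration at 5 of 20, the imputed maximum (1.43) is nearer the complete-data value (1.37) than the recorded one (1.23). The evidence on extremes is therefore mixed. It shows that extremes depend on how many parabolas were seen, which is a reason to report counts.
- Participants cites backup personnel for dropouts. A replacement could reduce the loss, though the article does not say how this would work in flight.

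These points limit the claim but do not rescue the sentence. If it covers signals, it puts model output into a description of measurements. If it covers a person-level variable, it borrows from at most three other people. Under either reading, nothing in the article says that signals are exempt.

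**Conclusion.** The point holds as a moderate one. The Analysis section pairs an available-data rule with an unscoped imputation rule and does not say which governs lost signal. In a four-person, primarily descriptive study the second rule has little purpose, and it leaves a route for model-generated values into the primary description.

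The possible size is 75% of one participant's data and 15 of 90 parabolas (16.7%) for a stop after 5 of 20. For stops after 1 to 15 parabolas it runs from 95% to 25% of that participant's data and from 21.1% to 5.6% of all parabolas. These figures assume that one of participants 2 to 4 stops early, that nobody takes over, and that whole parabolas are imputed. The article states none of these. If no data are lost, no harm arises. The exploratory aim and the inferred link to the signals are why the point is not rated higher.

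**What to change.** Replace the imputation sentence in the Analysis section. State that signal and waveform data are summarised as recorded, without imputation, and that each summary is accompanied by the number of parabolas and beats per participant and gravity phase, with reasons for any loss. Drop multiple imputation, or limit it to non-signal variables listed by name. The available-data rule for early termination can stay as it is.

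A sensitivity comparison between participants on matching parabola positions is not recommended. Under Schedule and Table 1, participant 1 is measured only on the last 10 parabolas of each flight and participants 2 to 4 only on the first 20, so participant 1 shares no position with anyone. Such a comparison would leave out 30 of the 90 parabolas.

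The cost is about one sentence of text and a table of counts. No change to data collection is needed.

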## Results

ARTIFACTS is an experiment within the AuRelia project. AuRelia has been funded since August 2023 by the German Federal Ministry of Economics and Climate, funding code FKZ:50RP2350. Additional institutional resources are used.

The data will be collected entirely and exclusively during the parabolic flights, which will take place between September 2024 and July 2025. As of June 2024, no data sets have been collected yet. Data analysis will take place until December 2025. The publication of results is planned for June 2026.

A total of 4 participants have been recruited (3 male and 1 female). The study’s primary end point involves characterizing acceleration artifacts, including their morphology and expression, analyzing variations in acceleration, and identifying factors influencing acceleration sensors under gravitational acceleration. The secondary end points encompass the assessment of signal filtering and peak detection algorithms. A multimodal data set will be available that serves as the foundation for research into a noninvasive and gentle method of BCG-SCG using 6-DOF sensors (3D gyroscopes and 3D accelerometers). This research explores hypotheses regarding the formation, detection, and mitigation of acceleration artifacts arising from the intrinsic rotation of BCG-SCG sensors and their differentiation from heart-induced sensor accelerations. The collection of the multimodal basic data set provides the necessary basis for research into a noninvasive and gentle method of BCG-SCG with the aid of low-noise and synchronous 6-DOF sensors. This research contributes fundamental findings for unambiguous characterization based on compensated location vectors. It also helps develop methods for integrating signal characterization on resource-limited sensors and translational models for mapping between BCG-SCG and reference methods.

## Discussion

### Prior Work

To our knowledge, prior work on BCG-SCG signals has not considered acceleration bias caused by gravitational influences on the self-rotation of acceleration sensors. However, we found several studies in our literature that address the participant of motion artifacts in BCG and potential countermeasures [19-21]. Also, we identified 2 publications considering BCG measurements under parabolic flight conditions, which address highly artifact-biased data sets but without explaining the kind or source for the artifacts [22,23].

### Anticipated Findings

This study will have shown that artifacts in BCG-SCG signals caused by the roll, pitch, and yaw movements of accelerometers in relation to the earth’s gravity can be detected and eliminated from BCG-SCG signals, and these signals can thus be characterized more precisely. In the context of the use of multimodal measurement systems in this study, uncertainties in using these are expected to become apparent. However, this demonstration is not the aim of the study. Thus, the study provides insights into the uncertainty of multimodal measurement systems.

### Interpretations and Implications

Our study will provide a basis for using more clearly characterized BCG-SCG signals in future studies and applications. In future studies in which BCG-SCG signals are to be evaluated, more reliable evaluations can thus be made. The precise signal characterization will also be of clinical relevance in the future. According to [24], monitoring by SCG and associated applications is still only possible to a very limited extent due to artifacts in the signal. Through a good characterization of BCG-SCG signals, BCG-SCG could be used more reliably than before for the diagnosis of diseases such as heart disease and the monitoring of heart health. Based on the findings of this study, clinical applications for diagnostics using BCG-SCG can be further developed.

### Strengths and Limitations

A strength of this study is that investigating artifacts in BCG-SCG signals using different gravity states is a pragmatic approach to improving signal characterization. A small sample is sufficient to obtain fundamental findings. Matching BCG-SCG signals with reference methods such as ECG is fundamental for subsequent studies on how ECG and BCG-SCG can complement each other. Although it is assumed that the scope of the study is sufficient to characterize the BCG-SCG signals as planned, even longer sensory measurements in different gravitational states could possibly further improve signal characterization. In this study, the accelerations caused by the movement of the accelerometers in relation to the earth’s gravity are distinguished. Generally, valid statements about heart-induced sensor accelerations cannot be made because of the small and diverse sample size. However, because this is not the aim of this study, it is not a limitation in the strict sense.

### Future Directions

Future studies can test how well the findings from this study regarding the detection and removal of artifacts can be transferred to BCG-SCG signals recorded over more extended periods under normal terrestrial gravity conditions. In addition, various test conditions can be used to investigate how precisely the artifacts can be detected and how they can be removed from the signal, even when the respective sensor is in different positions due to various everyday body postures (such as lying down or bending over). In addition to the artifacts examined in this study, artifacts may arise from other sources (eg, internal body movements caused by speech or external movements such as passing vehicles). Artifacts coming from different sources are not always easy to distinguish. As a result, it is not always possible to identify which source leads to strong artifacts. Knowing this may help determine under which circumstances BCG-SCG signals can be best characterized and thus should be recorded, which could be investigated in future studies.

### Conclusions

ARTIFACTS is fundamental research, the findings of which will contribute to precise signal characterization based on compensated position vectors. It also provides insights into the uncertainties of multimodal measurement systems and develops methods for integrating characterization on resource-limited sensors and translational models for mapping between BCG-SCG and reference methods, namely, echocardiography, phonocardiography, and electrocardiography. Taken together, a portfolio of methods will be available as a scientific basis for further research to enable cost-effective wearables with a wide range of applications for outpatient diagnostics and monitoring in prevention, health promotion, and diagnostics.

## Abbreviations

BCG: ballistocardiography
DFG: German Research Foundation
6-DOF: 6 degrees of freedom
ECG: electrocardiogram
GDPR: General Data Protection Regulation
SCG: seismocardiography
TUHH: Hamburg University of Technology
